#### 12.4. PREGNANCIES

Although not considered serious adverse events, if a woman becomes pregnant in the During a clinical trial, the principal investigator or a collaborator should inform the sponsor and monitor of the clinical trial. In case of pregnancy, it will be followed until its end, as well as the newborn until it reaches one year of age.

#### 12.5. RECORDING AND REPORTING OF ADVERSE EVENTS

##### 12.5.1. NON-SERIOUS ADVERSE EVENTS

All AEs should be recorded and documented in the patient's medical history and in the data collection notebook using standard medical terminology, avoiding the use of ambiguous or colloquial expressions. The dates of commencement and resolution, the severity and the severity of any adverse event, as well as its relationship to the study drug or procedure. The AE and SAEs will be monitored until they are completely resolved adding if necessary, a safety period of 30 days once the subject has completed the study, at the discretion of the principal investigator.

The severity, severity and causal relationship of the AE (unrelated, unlikely, possible, probable, certain) shall be assessed in accordance with the guidelines specified in paragraphs 12.2 and 12.3. Measures taken and results obtained (e.g. hospitalization, withdrawal of treatment, etc.) of any adverse events should also be noted. AEs that are likely to be unrelated to the procedure (i.e., reported as unrelated) will not be considered adverse reactions to cell therapy in toxicity analyses and will be reported independently.

#### 12.5.2. SERIOUS ADVERSE EVENTS

If a SAE occurs, whether or not it is related to the study drug and whether or not the investigational product has been administered, the investigator will notify the sponsor within 24 hours of the time the site becomes aware of it by fax, email or email.

exceptionally telephone call through the SAEs notification form. The date and signature of the responsible investigator or one of his or her authorized staff members must appear on all notification reports. If you have any concerns regarding SAEs, or any concerns regarding the safety of the subject, please contact the sponsor's pharmacovigilance team:

[name] / [name]

Andalusian Network for the Design and Translation of Advanced Therapies - Junta de Andalucía

Serious adverse events that occur at any time after the patient's inclusion in the study should be reported, i.e. from the signing of the informed consent by the subject and up to 30 days after the patient has completed or left the study. A subject is considered to have completed the study after the last protocol scheduled visit or last contact with the investigator. The date of withdrawal or abandonment will be the date on which the patient and/or investigator determine that the subject can no longer comply with the protocol.

The sponsor shall be responsible for reporting suspected unexpected serious adverse reactions (SUAR) to the investigational medicinal product in accordance with applicable regulations. The reference for determining the expectability of the adverse reaction shall be the baseline safety information contained in the most recent version of the Investigator's Manual. It should be noted that SUARs that have not been previously documented in the Investigator's manual, or that occur

in a more serious form than expected (i.e. they are [unexpected]), are subject to prompt communication to the Regulatory Authorities by the Promoter.

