##### Safety:

- Incidence of AE, SAE, AR, as well as SUAR, throughout the intervention period in patients in the experimental group, as well as in the 12 months after the end of treatment, compared to the control group.

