### 8.2. WITHDRAWAL CRITERIA AND PLANNED ANALYSIS OF WITHDRAWALS AND ABANDONMENTS

Inclusion is defined as obtaining the subject's consent to participate in the study, regardless of whether eligibility is confirmed. Patients who have been included will discontinue their participation in the clinical trial if any of the following occur:

- Presence of a serious adverse event since inclusion that, in the opinion of the investigator or sponsor, may jeopardize patient safety or affect the results of the trial.
- Abnormal laboratory value(s), whenever in the opinion of the investigator and/or sponsor the safety of the patient is at risk or may interfere with the interpretation of the results of the study.
- Poor evolution or clinical conditions of the patient that prevent its continuity.
- Indication of prohibited medications or rescue therapies in case of poor wound evolution.
- Technical difficulties in the provision of the investigational drug. In this case, the patient may be re-evaluated when adequate production is possible. The patient will keep his or her assignment number in this case.
- When the patient does not cooperate or does not meet the requirements of the study.
- Withdrawal of consent or loss of follow-up by the patient.
- Pregnancy.

The patient has the right to discontinue the study at any time and any patient may be withdrawn from the study for any reason beneficial to their well-being. If, during the study, the patient's evolution makes it advisable to apply rescue therapies with proven efficacy, the patient will automatically leave the trial, and a failure of the therapy will be recorded in the course of the study will be treated within the guideline that the clinical experts and the health authorities decide.

For the purposes of the safety objective of the trial, safety follow-up of enrolled and withdrawn patients should be ensured throughout the duration of the clinical trial (12 months), to the extent possible. In any case, the date and reason why a subject discontinues participation in the clinical trial should be recorded in the Data Collection Notebook, and the sponsor should be notified immediately if the discontinuation is due to a Serious Adverse Event.

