#### Safety:

Incidence of AE, SAE, AR, as well as SUAR, throughout the intervention period, as well as the 12 months after the end of treatment

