- Any other major medical conditions (i.e., major adverse events that are not immediately life-threatening and do not result in death or hospitalization but may be life-threatening or may require intervention to prevent another of the outcomes listed above, e.g., cancer) according to appropriate medical criteria.
- Suspected transmission of an infectious agent through a drug.

Serious and unexpected adverse reaction (SUAR): A serious adverse reaction whose nature, severity or outcome is not consistent with the baseline safety information.

Toxic death is defined as death secondary to toxicity. This must be specified on the death report form: the cause of death must be listed as [toxicity]. The assessment of toxic deaths is independent of the assessment of response (patients may die from toxicity after a complete assessment of response to treatment).

Hospitalization is defined as the official admission to a hospital for a period of more than 24 hours. Hospitalization and prolongation of hospitalization are criteria for the severity of an AE; however, they are not considered by themselves a SAE. If there is no AA, the investigator should not report hospitalization or prolongation of hospitalization as a SAE. This is the case in the following situations:

- Hospitalization or prolongation of a hospitalization is needed to perform a procedure required by the protocol.
- Hospitalization or prolongation of a hospitalization is part of a routine procedure of the center (e.g., removal of a vascular stent after surgery).
- Hospitalization due to a pre-existing condition that has not worsened.

All AEs and SAEs suffered by subjects from the signing of the informed consent until the end of their participation in the study should be recorded.

The investigator or his or her collaborator will question and/or examine the patient for signs of adverse events. Questioning of patients regarding the possible occurrence of adverse events should be done in a general way (e.g., "How it has been felt since the last visit?"). The patient should not be questioned about the presence or absence of specific adverse events.

Promoter: Andalusian Network of Design and Translation in Advanced Therapies - Andalusian Public Foundation Progress and Health M. P.

SERIOUS ADVERSE EVENTS MUST BE REPORTED IMMEDIATELY, WITHIN 24 HOURS AFTER THEIR OCCURRENCE TO THE SPONSOR ACCORDING TO THE PROCEDURE DETAILED IN THIS PROTOCOL.

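### The protocol sets contradictory safety-collection windows for withdrawn and rescued patients: 12 months in section 8.2 and the main safety variable, but end of participation or 30 days after leaving in section 12

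*Protocol*

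**What the plan says.** Two places in the protocol set a long window.

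- Section 1.11 defines the safety part of the main variable as the incidence of AE, SAE, AR and SUAR during the intervention period, "as well as in the 12 months after the end of treatment, compared to the control group". Section 10.1 repeats the period: "throughout the intervention period, as well as the 12 months after the end of treatment".
- Section 8.2 ties the follow-up of leavers to the safety objective: "safety follow-up of enrolled and withdrawn patients should be ensured throughout the duration of the clinical trial (12 months"), qualified by as far as possible.

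Two places in section 12 set a shorter one.

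- Section 12.2 limits the recording of AEs and SAEs to the period "from the signing of the informed consent until the end of their participation in the study should be recorded". It does not define when participation ends.
- Section 12.5.2 requires SAE reporting from consent "up to 30 days after the patient has completed or left the study". It then fixes the day of leaving by a test of compliance with the protocol: "The date of withdrawal or abandonment will be the date on which the patient and/or investigator determine that the subject can no longer comply with".

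Section 8.2 also lists the reasons for discontinuing. Among them are an SAE, abnormal laboratory values, poor evolution, prohibited medication and rescue therapy. For a patient whose course makes rescue advisable it says "the patient will automatically leave the trial".

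**The concern.** Section 8.2 states what follow-up is wanted. Section 12 tells the site what to enter and what to send to the sponsor. For a patient who leaves early the two give different end dates, and the protocol does not say which prevails. A site can comply with section 12 to the letter and still not deliver what section 8.2 and the main variable need.

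Three features make this more than untidy wording.

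- **The affected variable is primary.** Event incidence over 12 months is half of the main objective.
- **Exit is not random.** Several listed reasons for leaving relate to the patient's condition, and rescue forces exit. If such exits are more frequent in one arm, that arm's observation would be cut short more often and its incidence would look lower. The trial is open-label with 10 patients planned per arm, so a few exits can matter.
- **Analysis cannot repair it.** An analysis plan can handle unequal follow-up time, but it cannot recover events that nobody wrote down. A late related event in a patient who received cells would also be relevant to the stopping counts in section 8.4, which are low: three patients with related serious toxicity, three with serious procedure-related infection, or one related death.

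**Working it through.** The protocol gives no figure of its own to reproduce here, so the check is window arithmetic on section 12 read alone.

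**Inputs**

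- Treatment starts on day 0 and the fourth dose is on day 21 (section 7, visits 2 and 5). Controls keep the same visit schedule.
- The safety window runs to 12 months after treatment (sections 1.11 and 10.1). Taking 12 months as 365 days, it ends on day 21 + 365 = 386.
- SAE reporting ends 30 days after leaving (section 12.5.2).
- Recording ends with participation (section 12.2). If participation ends on the day of exit, no later time is covered.

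**Formulas for a patient who had treatment to day 21 and exits on day t**

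- Days outside SAE reporting = 386 − (t + 30) = 356 − t, and never below 0.
- Days outside AE recording = 386 − t.
- Each is divided by 386 to give a share of the whole window. The SAE gap is also divided by 386 − t to give a share of the time left after exit.

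| Exit day | Outside SAE reporting | Share of whole window | Share of time left | Outside AE recording (12.2 at its strictest) |
|---|---|---|---|---|
| 28 | 328 days | 328/386 = 85.0% | 328/358 = 91.6% | 358/386 = 92.7% |
| 84 | 272 days | 272/386 = 70.5% | 272/302 = 90.1% | 302/386 = 78.2% |
| 180 | 176 days | 176/386 = 45.6% | 176/206 = 85.4% | 206/386 = 53.4% |
| 300 | 56 days | 56/386 = 14.5% | 56/86 = 65.1% | 86/386 = 22.3% |
| 356 | 0 days | 0% | 0% | 30/386 = 7.8% |

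For any exit before day 326, more than half of the time left falls outside SAE reporting (at day 326 it is 30 of 60 days).

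**Per arm.** With 10 patients, an arm has 10 × 386 = 3,860 planned safety days. One exit on day 28 takes 328/3,860 = 8.5% of them out of SAE reporting.

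**Completers.** Their 30 days begin after the last scheduled visit, so SAE reporting extends past day 386 and nothing is lost.

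**Under section 8.2.** If its 12-month follow-up governs recording and reporting, the planned gap is 0 days for every exit day. What remains is only what the qualifier allows, such as lost contact or withdrawn consent.

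**Does other text close the gap?** Section 8.2 follows a patient withdrawn for an SAE until that event resolves or is judged permanent. Section 12.5.1 follows AEs and SAEs to resolution. Both concern events already open and say nothing about new ones. Section 7 gives no separate contact schedule for withdrawn patients.

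**The case against.** The strongest reply is that section 8.2 speaks to exactly this group and this objective, and asks for 12 months. Section 7 adds that all patients should complete 12 months after the last administration. Nothing says that section 12 takes precedence. The undefined end of participation in 12.2 could be read as the end of the safety follow-up required by 8.2. Section 12.6 obliges the sponsor to notify every suspected serious unexpected reaction it knows of, without a 30-day limit, and the counts in section 8.4 have no time limit either. Some listed reasons for leaving are unrelated to risk, such as production problems, pregnancy or non-cooperation, and no reporting rule recovers a patient lost to follow-up.

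Much of this stands. A reader might infer that late events in withdrawn patients are never captured, that most late events are lost, or that they never reach the sponsor. The documents do not support those readings. Section 8.2 plans the follow-up, and a site acting on it may well record and send what it finds. The percentages above are shares of time. Turning them into shares of events would need an event rate over time, which the protocol does not give. Nor does it give withdrawal rates by arm, so no direction or size of bias can be stated.

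What does not stand is the claim that the texts can be fully reconciled by reading. The benign reading of 12.2 is available, but 12.5.2 blocks the same reading for SAEs: it dates leaving to the day the patient can no longer comply, and a rescued patient leaves automatically under 8.2. From that day the 30-day clock runs, whatever follow-up continues. The duties in section 12.6 depend on the sponsor having been told.

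**Conclusion.** The point holds as an internal contradiction. For patients who withdraw or are rescued, the main safety variable and section 8.2 call for 12 months, while 12.2 and 12.5.2 close recording at the end of participation and SAE reporting 30 days after leaving. Under section 12 read alone, exit on day 28 leaves 85% of the safety window outside SAE reporting, and exit on day 84 leaves 70%. Under section 8.2 the planned gap is zero. The size therefore depends on which section a site follows. It also assumes that 12 months is 365 days and that the patient was treated to day 21.

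The consequence is a risk, not a demonstrated loss: late new events in these patients may go unrecorded and unreported, and the loss could differ between arms because exit is partly tied to outcome. Completers are unaffected. This should be fixed because it touches a primary between-arm comparison and costs little. It does not show that the protocol set out to stop collecting safety data.

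**What to change.** Reconcile the sections by changing two of them.

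- **Section 12.2:** replace the end of participation as the limit for recording AEs and SAEs with the end of the 12-month safety follow-up, for every patient, including those withdrawn or rescued.
- **Section 12.5.2:** run SAE reporting to the same point, plus the existing 30 days. State that the date of withdrawal does not start the 30-day clock.
- **In both:** only withdrawal of consent to follow-up or loss of contact ends the window early. Record the date and reason, so that each patient's actual observation time is known.

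The change concerns recording and reporting only. It needs no change to study treatment, withdrawal criteria or rescue rules.

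The cost is a wording amendment and some extra site contacts for withdrawn patients, which section 8.2 already asks for.

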### 12.5.3. OVERDOSE

If an overdose is known or suspected to have occurred with the study drug, exceeding the dose indicated in the protocol, whether it is associated with an adverse event, the investigator should inform the sponsor.

If the overdose does not produce clinical sequelae, it will not be considered as a adverse event. Any clinical sequelae associated with overdose should be considered an adverse event (as described in section 12.5.1) or a serious adverse event (12.5.2). Signs and symptoms, clinical management, and outcome should be reported, if available. An overdose of the investigational product will be considered a SAEA if it is associated with any serious adverse events.

### 12.6. EXPEDITED NOTIFICATION OF RAGI

The sponsor shall notify the Spanish Agency of Medicines and Health Products of all suspected serious and, at the same time, unexpected adverse reactions associated with the medicinal products in question. research of which you have been aware, which have occurred in the clinical trial, whether they occur in Spain or in other countries. In all cases, such notification shall be made through the European database Eudravigilance\_CTM.

Notification of serious and unexpected adverse reactions by the sponsor to the Agency

The Spanish Association of Medicines and Medical Devices shall in all cases comply with the criteria and procedure specified in Articles 42, 45 and 46 of Regulation (EU) No 536/2014 of the European Parliament and of the Council of 16 April 2014.

Notification will be made in accordance with ICH E2A Definitions and Standards for Expedited Reporting.

## 13. ETHICAL ASPECTS

### 13.1. GENERAL CONSIDERATIONS

The sponsor and coordinating investigator of the trial will present to the reference REIC and the Committees of The research of the centers participating in this protocol and all related materials provided to the subject (such as subject information sheets or study descriptions used to obtain informed consent), as well as any compensation provided to the patient. The approval of the aforementioned Committee and the Spanish Agency must be obtained

of the Drug before starting the study and must be documented in a letter to the investigator, specifying the date on which the Investigators met and granting their approval. The investigator must also submit for evaluation by the CEIm and the AEMPS any modifications made to the protocol after receiving approval, in accordance with local legal procedures and requirements.

The trial will be conducted in accordance with the protocol following the sponsor's standard operating procedures and those established at the participating hospital.

The Trial will be conducted in accordance with the recommendations for Clinical Trials and evaluation of A product in the human research phase, which appear in the Declaration of Helsinki, revised in successive world assemblies (WMA, 2013), and the current Spanish Legislation on Clinical Trials (RD 1090/2015). The ICH-GCP (CPMP/ICH/135/95) standards will be followed.

The investigational product meets the definition of "investigational advanced therapy medicine " in Regulation (EC) No 1394/2007 of the European Parliament and of the Council

### 13.2. STUDY MONITORING

The monitoring will be carried out by personnel belonging to the Coordination Unit of the promoter itself. The responsible monitor will regularly contact and visit the investigator and will be allowed to inspect the various trial registries (CRDs and other relevant data) and source documents, if patient confidentiality is maintained, in accordance with local requirements. The monitor will be responsible for inspecting the CRDs at regular intervals during the study, to Verify compliance with the protocol and that the data included is complete, consistent and accurate. The monitor must have access to lab test reports and other records of patients who are necessary to verify the information included in the CRD. The investigator (or his/her representative) agrees to cooperate with the monitor to ensure that all problems identified in the course of these monitoring visits are resolved. 100% of the data collected will be monitored.

### 13.3. RETENTION OF STUDY DOCUMENTATION

The Investigator must maintain an adequate and accurate record to allow the study to be fully documented and for the study data to be verified later.

Notification of the termination of the Clinical Trial or premature termination of the Trial will be given in accordance with the requirements described in Article 30 of Royal Decree 1090/2015, of 24 December, which regulates clinical trials with medicines, the Committees for Research Ethics with Medicines and the Spanish Register of Clinical Studies. All documentation related to the clinical rehearsal will be archived in the custody of the Primary Care Unit (UA) of the Granada Metropolitan District , according to current legislation.

#### 13.4. TRIAL INSURANCE

The Andalusian Public Foundation for Progress and Health, as the promoter of the study, has, in accordance with Spanish legislation, civil liability insurance. This policy covers all possible damages that the subject may suffer as a result of the administration of the product under study, in accordance with current legislation (RD1090/2015, article 9).

#### 14. DATA COLLECTION NOTEBOOKS

Investigators, or an authorized representative of the study team, must complete a CRD for each patient enrolled in the study. This also applies to records of patients who do not complete the study. If a patient withdraws from the study, the reason must be indicated in the CRD. If a patient withdraws from the study due to a treatment-limiting adverse event, every effort should be made to clearly document the outcome.

#### 15. FOLLOW-UP AND FINAL REPORTS AND COMMUNICATION OF RESULTS

The principal investigator undertakes to submit the follow-up and final reports, within the deadlines established and communicate, where appropriate, the interruption and the reasons for it. The results of this study will be analyzed and may be published or disseminated in medical journals and/or meetings

scientific. The publications generated will be presented to a committee for the drafting of the study, which will also include the promoters, and the rest of the researchers involved in the study. Since major medical journals restrict, in some cases, the number of authors, the selection of researchers will be based on the recruitment rate and/or tasks performed during the study.

After 12-month follow-up of the patients, the database will be closed and analyzed. Trial data will be published as described above.

